
### Approach

By employing complementary data sources—including data from analysis of drug samples, quantitative intake and post-test surveys, SCS, coroners, paramedic services, and qualitative interviews—this study will comprehensively evaluate the impact of DCS on a range of policy-relevant drug-related outcomes, while considering the impacts of co-located SCS (refer to Table 1: Measures, Outcomes, and Data Sources). A mixed-methods approach followed by a meta-inference process will be used to maximize multiple data sources and synthesize results of quantitative and qualitative analyses.

**Table 1 Tab1:** Measures, outcomes, and data sources

Measures and outcomes	Data sources
Aim 1: Evaluate the impact of DCS access on changes in and factors influencing overdose and related risk behaviors	
Self-reported overdose among those that access DCS and those that do not	– Quantitative survey data (intake) – SCS client data
Proportion of participants reporting increase in protective behaviors (not using alone, carrying naloxone, use of SCS, consultation with staff, smaller/) “tester” dosage, discarding toxic substances)	– Quantitative survey data (intake/post-test) – SCS client data
Proportion of participants reporting they gained, intend to use, and/or used knowledge and skills	– Quantitative survey data (post-test) – Qualitative interviews
Aim 2: Investigate the perceived capacity of DCS to prevent overdose	
Characterize participant perceptions on the capacity of DCS to alter the risk of overdose	– Qualitative interviews
Identify participant perceptions of contexts, facilitators, and barriers to the use of DCS	– Qualitative interviews
Aim 3: Identify trends in the composition (qualitative and quantitative) of the unregulated drug supply in Toronto	
Number of analysis results detecting composition different from participant expectations	– Quantitative survey data (intake) – Drug sample analysis data
Increase in accuracy and timeliness of alerts in response to dangerous drug trends	– Drug sample analysis data – Qualitative interviews
Spatial association between frontline harm reduction agencies with DCS and fatal overdose, and changes over time	– First responder and coroner data (from OCC and TPaS)

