### Data collection

#### Intake and post-test surveys (Aim 1)

Intake and post-test surveys will be administered to all consenting DCS clients at the three sites in Toronto, including participants who access DCS once and those who access DCS multiple times, allowing for a combined use of cross-sectional and longitudinal approaches. Surveys will be administered by frontline staff on an electronic tablet with the option for self-administration depending on the needs of the participant. Guided by the abovementioned conceptual framework, demographic and drug-using factors will be collected at first visit to DCS via a baseline intake survey to assess the influence of additional vulnerabilities facing key populations. An anonymous identifier will be created in the baseline intake survey and linked to intake surveys completed at subsequent visits. Questions on the intake survey, administered at every visit to DCS, include the following: What substance participants believe they are having tested?; When and where they purchased the substance?; and, If they are sharing the results with others, with how many people? Post-test surveys conducted immediately after analysis results are provided will query participants about their intended behaviors in response to analysis results, as well as allow frontline staff to record other services accessed (e.g., SCS, naloxone) and observed behaviors (e.g., discarding remainder of drug that was tested).

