### Analytic plan

#### Multivariable model of participant overdose risk behaviors (Aim 1)

For participant survey binary outcomes, we will employ either population-averaged models (i.e., generalized estimating equations; GEE) or subject-specific models (generalized linear mixed models; GLMM) with binomial distribution and logit link. The primary outcome is recent (i.e., past 6 months) self-reported overdose; the primary exposure is a categorical measure of frequency of DCS access over the past 6 months. GEE will be used if participant visits are equally distributed over time and if we have low levels of missing data. In the case of unequal distribution of participant visits over time and/or substantial missing data, we will employ GLMM. These models efficiently address problems of missing data and variable timing of subject visits. Both GEE and GLMM are suited to the analysis of longitudinal data, as they can account for both within-subject correlation and between-subject differences with results also remaining highly interpretable. We will initially model temporal correlations between subject responses using an autoregressive structure, with subject-specific variances and correlations assumed to decline exponentially over time; this is critical given that we anticipate variance in client follow-up times. GLMM models will also include independent time-varying variables from the linked intake and post-test surveys as potential confounders. This will allow for a “pre versus post” test evaluation using longitudinal DCS data. To assess potential bias as a result of loss to follow-up, sociodemographic and drug-related factors collected on the intake and post-test surveys will be compared among participants who only completed a baseline DCS visit and those that accessed the service repeatedly. Multilevel multiple imputations may also be considered if needed.

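### Adjusting the GLMM for post-test survey items conditions on consequences of drug checking, so the DCS coefficient is no longer its total effect on overdose

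*Protocol article*

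**What the plan says.** The section on the multivariable model for Aim 1 defines the analysis: "The primary outcome is recent (i.e., past 6 months) self-reported overdose", and "the primary exposure is a categorical measure of frequency of DCS access over the past 6 months". A GEE is planned if visits are evenly spread and little is missing; otherwise a GLMM is used. For the GLMM, "GLMM models will also include independent time-varying variables from the linked intake and post-test surveys as potential confounders". No variable is named and no lag is given.

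The section on intake and post-test surveys describes what the second survey holds. "Post-test surveys conducted immediately after analysis results are provided will query participants about their intended behaviors in response to analysis results", and staff also use it to "record other services accessed (e.g., SCS, naloxone) and observed behaviors (e.g., discarding remainder of drug that was tested".

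Table 1, under Approach, lists among the Aim 1 outcomes "Proportion of participants reporting increase in protective behaviors", with the intake and post-test surveys among its sources, and knowledge and skills gained or used, with the post-test survey as a source. It takes self-reported overdose from the intake survey and SCS client data.

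**The concern.** A confounder must not be a consequence of the exposure. The post-test items that the article describes are reactions to a drug-checking result, and the Conceptual framework section presents informed decisions and action before use as the way in which DCS would prevent overdose. The same survey thus supplies Aim 1 outcomes and adjustment variables for the Aim 1 primary model.

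At stake is the meaning of the primary estimate. The study's overall goal is to learn whether access to DCS is associated with less overdose, which calls for a total effect. Holding fixed what clients did after receiving results leaves a different quantity. It can also open a non-causal path, for example if higher-risk clients are more likely to accept naloxone.

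**Working it through.** **1. Timing.** Let t be the intake date of a survey record.

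- Outcome: overdose between t minus 6 months and t, asked at intake.
- Exposure: number of DCS visits, in categories, over the same 6 months.
- Post-test item from the same visit: recorded after t. The section on analysis of drug samples gives one to two business days for results, and even the shorter target of under 2 hours puts the post-test survey after intake.
- Post-test item from an earlier visit inside the window: recorded before t, but after a drug-checking result that counts toward the exposure.

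**2. Possible roles.**

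- An earlier-visit response item can lie on the path from DCS to overdose (mediator). It can also share an unmeasured cause with overdose (collider). It may influence later DCS use too; it is then a time-varying confounder affected by earlier exposure, which ordinary regression adjustment cannot handle. At a first visit no such value exists.
- A same-visit item comes after the intake-reported outcome window, so it can neither mediate nor confound. It can still distort the estimate if past overdose influences it.

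**3. Which branch.** The GLMM applies when visits are uneven or much is missing. The model section expects follow-up times to vary, the sample-size section describes passive recruitment, and the Limitations section says linkage depends on clients creating and consistently using an identifier. The GLMM is therefore the likely form.

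**4. Direction, by illustration.** The article gives no effect size, overdose rate or mediated share, so there is no plan figure to reproduce. All parameters below are assumptions. Single-record logistic data were simulated (n = 400,000) with an intake confounder C, exposure A, post-test item M and overdose Y:

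- logit P(A = 1) = −0.3 + 0.5C
- M = A + standard normal noise
- logit P(Y = 1) = −1.6 + 0.6C − 0.5(1 − s)A − 0.5sM, where s is the share of the effect that runs through M.

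The later rows of the table change this structure as labelled.

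| Assumed structure | OR for A, adjusting for C | OR for A, adjusting for C and M |
|---|---|---|
| s = 25% | 0.61 | 0.68 |
| s = 50% | 0.61 | 0.77 |
| s = 75% | 0.61 | 0.88 |
| s = 100% | 0.63 | 1.02 |
| s = 100%, M measured with noise | 0.62 | 0.78 |
| s = 50%, unmeasured cause shared by M and Y | 0.62 | 0.54 |
| Same-visit M, not influenced by Y | 0.60 | 0.61 |
| Same-visit M, influenced by Y | 0.60 | 0.27 |

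Hand check of the first four rows: with M in the model the OR should be exp(−0.5(1 − s)), which is exp(−0.375) = 0.69, exp(−0.25) = 0.78, exp(−0.125) = 0.88 and exp(0) = 1.00. The simulated values agree to within simulation error.

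Pure mediation moves the OR toward 1. A shared unmeasured cause, or an item influenced by past overdose, moves it away from 1.

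**The case against.** The case on the other side has four parts.

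- **Timing.** Because the outcome looks back 6 months from intake, a same-visit post-test item cannot be a mediator, and the article does not say whether covariates are lagged. This stands, and it limits the mediation argument to earlier visits. It does not rescue the adjustment, because a same-visit item cannot confound either.
- **Scope.** The sentence governs only the GLMM and names no variables. The model section also suggests that some post-test items are sociodemographic or drug-related factors. The final covariate list could sit in a document not shown, with the conceptual framework guiding the choice. It stands that not every post-test item need be a consequence of DCS. But the article does state a rule on where confounders come from, and the post-test content it describes consists of responses to DCS. That is a stated choice, not missing detail.
- **SCS use.** The article rightly treats co-located SCS as something to separate from DCS, and SCS opened first. The post-test survey is where staff record SCS access, so discarding the whole survey could lose useful information. This stands: SCS use before the exposure window belongs in the model as a confounder.
- **Size.** No input to the illustration comes from the documents. This stands, and the table shows direction only.

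**Conclusion.** The point holds for the GLMM form of the Aim 1 primary model. Post-test items that record responses to DCS are labelled as potential confounders although, on the article's own account, they follow the exposure and overlap with Aim 1 outcomes. Conditioning on them means that the DCS coefficient is not the total effect of access. This rests on the described response items being among those entered, and on the GLMM being the form used.

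A reader might infer more: that the primary model as a whole is affected, that the adjustment removes the DCS effect, or that the bias always runs toward no effect. The documents do not support these readings. The sentence does not cover the GEE. Complete removal needs the whole effect to pass through accurately measured post-test items. The bias is often toward the null but can go the other way, and its size cannot be derived from the article.

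**What to change.** - In the confounder sentence, remove the post-test survey as a source for items that record a response to DCS.
- Limit the primary adjustment set to baseline intake factors and to intake or SCS-cohort values, including prior SCS use, that precede the 6-month exposure window. An intake value from a preceding visit does not qualify merely because it is earlier: if that visit falls within the 6 months, it is part of the exposure.
- Analyze post-test behaviors as outcomes, in line with Table 1, or in a separately labelled mediation analysis.
- Where a time-varying confounder is affected by earlier DCS use, add a marginal structural model as a sensitivity analysis.

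No new data collection is required. The cost is a change of wording, a little more analysis work, and less use of visit-level service data in the primary model. Clients with a single visit have no earlier intake record, so for them adjustment will rest on baseline factors and, where they consent to linkage, SCS-cohort data.

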### Ethics, consent, and permissions

Research Ethics Board approval has been obtained for this research study from Providence St. Joseph’s and St. Michael’s Healthcare, Toronto Public Health, Centre for Addiction and Mental Health, and University of Toronto. Client provision of informed consent is integrated into the baseline intake survey, although clients that are unwilling or unable to provide informed consent will still be provided access to DCS. Data will be securely stored at St. Michael’s Hospital.

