### Limitations

The study has limitations typical of community-based intervention evaluations. Since denying access to DCS is not ethical or feasible, the recruitment process is being integrated directly into the delivery of DCS. While this will allow for the collection of data from a large proportion of the population of DCS clients, it does present limitations. For instance, it is not possible to estimate the number of individuals that will access DCS and provide data, nor the total person-time of data. Second, we note challenges in disentangling the impact of SCS and DCS on overdose incidence and related behaviors given that these two interventions will be co-located in our study setting. However, the 1-year delay between the implementation of SCS and that of DCS provides an ideal natural experiment to test the independent effects of these interventions. Further, the harmonization of data collection tools between SCS and DCS evaluations will further allow for the assessment of independent effects as we are able to evaluate outcomes among SCS clients who do and do not use DCS. Another limitation is the absence of a comparison group, except for the SCS sub-analysis. A final challenge worth noting is that while we would prefer that participants create an anonymous identifier, since this would allow us to link their data from separate visits to DCS and therefore employ panel approaches, this will depend upon the willingness of clients to consent to participating in the research, creating an anonymous identifier, and consistently recording their survey responses under their identifier at subsequent visits.

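### The loss-to-follow-up check cannot tell one-time clients from repeat clients whose visits were not linked

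*Protocol article*

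**What the plan says.** Four places in the protocol article bear on this point.

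- **Intake and post-test surveys (Aim 1)** ties the baseline record to first use of the service: "demographic and drug-using factors will be collected at first visit to DCS via a baseline intake survey". It describes linkage without conditions: "An anonymous identifier will be created in the baseline intake survey and linked to intake surveys completed at subsequent visits".
- **Ethics, consent, and permissions** places research consent inside that survey ("Client provision of informed consent is integrated into the baseline intake survey") and adds that "clients that are unwilling or unable to provide informed consent will still be provided access to DCS".
- **Limitations** is more guarded about linkage. The identifier is something the authors hope for ("while we would prefer that participants create an anonymous identifier"), and panel analysis depends on clients consenting, creating it and "consistently recording their survey responses under their identifier at subsequent visits".
- **Multivariable model of participant overdose risk behaviors (Aim 1)** assesses loss-to-follow-up bias with a two-group comparison, in which sociodemographic and drug-related factors "will be compared among participants who only completed a baseline DCS visit and those that accessed the service repeatedly". It names no third group for records that could not be linked. The primary exposure is a categorical frequency of DCS access over the past 6 months, and its source is not stated.

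**The concern.** The check needs two groups: people who came once, and people who came back. In the data, a returning client is recognised only through the identifier. If that client does not re-enter it, the visit looks like a new person with no follow-up. A client who was served without consent and joins the research later completes a baseline survey that is not a first visit.

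The baseline-only group then combines three kinds of record: true one-time clients, repeat clients whose visits were not linked, and clients with earlier unrecorded use. The comparison is meant to show whether people who drop out differ from those who stay. If part of the drop-out group consists of people who stayed, a finding of little difference is weak evidence that loss to follow-up is harmless.

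There is a second consequence. GEE and GLMM allow for within-subject correlation only among records that share an identifier. Any unlinked repeat record that enters the model counts as a separate person.

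**Working it through.** **The plan's own figure.** The only Aim 1 size figure is about 1080 DCS clients. The first step reproduces: 9000 × 0.20 = 1800. Then 1800 × 0.75 = 1350, and 1080 / 1350 = 0.80, a reduction whose size the article does not state. Here 1080 serves only as a scale; the shares below do not depend on it.

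**What is not given.** The article gives no linkage-failure rate or consent rate, and says the split between unique and repeat clients cannot be estimated in advance. Everything below is an illustration under assumed rates.

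**Step 1: repeat clients among apparent one-time records.** Let N = 1080, r = share of clients who truly return, k = total visits per returner, and u = probability that a return visit is not linked. Assume each unlinked return creates one new single-visit record.

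- True one-time records: N(1 − r)
- Single records from returners: M = N·r·(k − 1)·u + N·r·u^(k−1). The first term is duplicate records. The second is genuine first baselines whose returns all went unlinked.
- Share misfiled: f = M / [N(1 − r) + M]
- Apparent number of clients: N[1 + r(k − 1)u]

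| r | k | u | True one-time | Misfiled M | f | Apparent clients |
|---|---|---|---|---|---|---|
| 0.3 | 2 | 0.1 | 756 | 64.8 | 8% | 1112 |
| 0.5 | 4 | 0.1 | 540 | 162.5 | 23% | 1242 |
| 0.5 | 2 | 0.3 | 540 | 324 | 38% | 1242 |
| 0.7 | 4 | 0.5 | 324 | 1228.5 | 79% | 2214 |

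The first and last rows are the extremes over r = 0.3 to 0.7, k = 2 or 4, and u = 0.1 to 0.5.

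**Step 2: effect on the check.** If misfiled records resemble linked returners, a true difference D appears as (1 − f)·D. The four rows leave about 92%, 77%, 62% and 21% of D.

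**Step 3: late consent.** Suppose a share s declines at the first visit, and repeat users among them consent later. The share of baseline records with earlier DCS use is r·s / [(1 − r)(1 − s) + r].

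- r = 0.3, s = 0.1: 0.03 / 0.93 = 3%
- r = 0.7, s = 0.5: 0.35 / 0.85 = 41%

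**Step 4: exposure, only if frequency is counted from linked visits.** Assume 25% overdose risk in the unexposed and a true odds ratio of 0.60. The exposed odds are (0.25 / 0.75) × 0.60 = 0.20, a risk of 16.7%. If a share c of the apparent unexposed group is really exposed, its risk is (1 − c) × 0.25 + c × 0.167. The observed odds ratio becomes 0.63 (c = 0.10), 0.72 (c = 0.40) or 0.87 (c = 0.75), assuming non-differential misclassification. If frequency is self-reported, this step does not apply.

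**Step 5: what the fix leaves.** If all duplicate records report earlier use and are set aside, only the N·r·u^(k−1) term remains. For r = 0.5, k = 2, u = 0.3 that is 540 × 0.3 = 162 records, and 162 / (540 + 162) = 23%, down from 38%. For r = 0.5, k = 4, u = 0.1 it is 540 × 0.001, less than one record.

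**The case against.** The other side has several good arguments.

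- **The linkage problem is disclosed.** Limitations names all three dependencies: consent, an identifier, and its consistent use. This stands. But the disclosure concerns whether panel methods are possible, and it is not carried into the loss-to-follow-up comparison, which is written as if both groups were known.
- **The survey may already ask about earlier use.** The article lists only some of the questions, and the full questionnaire is not shown. This also stands, so the fix is conditional. The point rests on the comparison that the article does specify.
- **There is no rule for unlinked records.** True. That they fall into the baseline-only group is inferred from the two-group wording.
- **Late consent is hypothetical.** The article does not say that consent is sought again after a refusal. Step 3 is therefore a possibility, and failed linkage is the firmer ground.

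A reader might infer more than the documents support. One inference is that repeat users enter the main model as unexposed. That holds only if frequency is counted from linked visits; a self-reported frequency would still classify them as exposed, and the source is not stated. Another is that the pre-versus-post "test evaluation using longitudinal DCS data" uses contaminated baselines as its pre state. The sentence follows a reference to linked intake and post-test surveys and may mean intake against post-test; baseline is never named as the DCS-naive state. A third is that the check must come out reassuring. Step 2 shows dilution, not disappearance, and clients who avoid identifiers may differ from linked returners, so even the direction is not certain.

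**Conclusion.** The point holds in a narrow form. Because the service is given without research consent and the identifier is optional, neither a first visit nor a one-time client can be read from a baseline-only record. The specified check cannot separate drop-out from failed linkage. Its dilution towards no difference depends on misfiled records resembling linked returners. Unlinked repeat records would also count as separate people in the GEE or GLMM.

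The size is unknown. The 8% to 79% range shows only that modest to large effects are compatible with assumed rates; it does not estimate this study. Bias in the primary exposure, or in a pre/post contrast, is conditional on choices the article does not state and is not established here. The change is worth making because earlier use that is not asked about at intake cannot be recovered later from anonymous, unlinked records.

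**What to change.** 1. At every intake, including baseline, ask whether the client has used any of the three DCS sites before, and how many times in the past 6 months, if the survey does not already ask this. Take the exposure frequency from the answer and say so in the analytic plan.
2. In the loss-to-follow-up check, put records without an identifier, and baselines reporting earlier DCS use, in a separate category (unlinked or previously exposed) outside the one-time group. Report its size.
3. Add a sensitivity analysis of the main model, and of any pre/post contrast based on baseline records, restricted to baselines with no earlier DCS use.
4. State the residual limitation: a returner whose later visits all go unlinked still looks like a one-time client. The new questions also do not link duplicate records in the main analysis.

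The cost is one or two items on an existing tablet survey and a few sentences in the plan. Frequency will rely on recall, though the primary outcome is already a 6-month self-report, and some baselines will leave the comparison.
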